#### Dermatology life quality index

2.5.2

According to the DLQI questionnaire,^[16]^ patients need to complete ten questions about the impact of the disease on their quality of life (0 = none; 1 = slight; 2 = serious; 3 = very serious). The DLQI scores are calculated by summing the scores for each question. The maximum value is 30, and the minimum value is zero. The higher the scores, the greater the impact on the quality of life.

#### Laboratory indicator

2.5.3

Using the IBM SPSS Statistics (version 22.0) random number generator, 22 patients will be selected from each group to detect serum VEGF, TNF-α, IL-23, and IL-17 levels before and after the second week of treatment.

#### Confocal laser scanning microscope

2.5.4

Patients in each group underwent in confocal laser scanning microscope before and after the second week of treatment.

### Safety evaluation

2.6

According to the safety assessment in randomized controlled clinical trials,^[17]^ the safety of this study will be evaluated by adverse events, routine blood tests, and liver and kidney function tests.

### Data collection and management

2.7

All data will be analyzed according to the intention to treat principle. The missing value will be dealt with by carrying forward the most recent observation to the end point.

This study will use the IBM SPSS Statistics (version 22.0) software for data management and analysis. Professionally-trained dermatologists will collect all data. Members of the research team will perform the data collection and statistical analyses. Quantitative indicators will be expressed as mean ± standard deviation. If the sample is normally distributed and the variance is uniform, the *t* test will be performed: the paired sample *t* test will be used for intra-group comparison, and the independent sample *t* test will be used for inter-group comparison. If the variance is uneven, the approximate *t* test will be used. If the sample is not normally distributed, the rank-sum test (non-parametric) will be applied. The Chi-square test will be used for counting data. *P* values less than .05 will be considered as statistically significant.

The Chinese Ethics Committee of Registering Clinical Trials (Chengdu, China), which does not have any competing interests, will be responsible for monitoring the data. The Department of Science Research of the hospital at Chengdu University of TCM, which is independent of the investigators, will perform data audits in the trial.

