**Conclusion::**

This study will evaluate the efficacy and safety of various Chinese herbal bath conditions (water temperatures and herbal concentrations) on the treatment of psoriasis vulgaris, which will provide an important reference for the operation of Chinese herbal bath.

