#### Sample size calculation

2.2.3

According to the calculation formula of sample size in clinical trials,^[7]^ the necessary estimated loss rate is 10%, and the total sample size is 288 cases, with 36 cases per group. There will be 36 participants assigned to each group, including 36 cases in the basic treatment group, 36 cases in the control group, and 36 cases in each of the 6 observation groups.

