#### The effective rate of treatment, pruritus score, and incidence of adverse reactions

2.5.1

The Guiding Principles for Clinical Research of New Traditional Chinese Medicine (trial) is the general evaluation standard in China. According to the evaluation standard, the effective rate of treatment, pruritus score, and incidence of adverse reactions are taken as secondary outcomes.^[15]^

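### The intention-to-treat and carry-forward rules cover all data without a safety exception, so harm of a bath condition can be slightly understated if some patients never take the assigned bath

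*Protocol article*

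**What the plan says.** Section 2.7 (Data collection and management) opens with the analysis principle: "All data will be analyzed according to the intention to treat principle". The next sentence sets the missing-data rule: "The missing value will be dealt with by carrying forward the most recent observation to the end point". Neither is limited to efficacy.

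The trial's data include safety data. Section 2.5.1 says that "the effective rate of treatment, pruritus score, and incidence of adverse reactions are taken as secondary outcomes". Section 2.6 says that "the safety of this study will be evaluated by adverse events, routine blood tests, and liver and kidney function tests"; it names no analysis set and no grouping rule. The abstract's conclusion makes safety by condition an aim: "This study will evaluate the efficacy and safety of various Chinese herbal bath conditions (water temperatures and herbal concentrations".

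Four other places bear on the point:
- Section 2.2.6 states that blinding is not applicable, so patients know their assignment.
- Section 2.2.3 allows for loss: "the necessary estimated loss rate is 10" per cent, and "the total sample size is 288 cases, with 36 cases per group".
- Section 2.3.5 has a nurse prepare each bath and set its temperature, once a day for 2 weeks. It describes no change of setting.
- Section 2.3.1 gives every patient the basic treatment, which is two oral products and a topical oil.

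**The concern.** Intention to treat suits the PASI comparison, because it keeps the randomised groups intact. The safety question is different: what does a given temperature and concentration do to those who bathe in it? A patient who is randomised to a bath but never takes it cannot have a reaction to that bath, yet counts in its denominator.

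Carry-forward raises a similar problem for laboratory safety. If a patient leaves before any post-treatment blood test, the most recent observation is the baseline value. Carrying it to the end point records no change, whatever happened in between.

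At stake is how accurately reaction rates and laboratory changes are reported for each bath condition, in arms of only 36.

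**Working it through.** **Reading the rule.** Section 2.7 covers all data, section 2.5.1 makes adverse reactions an outcome, and section 2.6 makes laboratory tests part of the safety evaluation. Neither 2.5.1 nor 2.6 sets a different population. On the ordinary meaning of the words, safety is analysed by assignment with carry-forward.

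**The plan's own figure.** 8 groups × 36 = 288, which matches the stated total. 32 / (1 − 0.10) = 35.6, rounded up to 36, so 36 is consistent with 32 evaluable per group. The article does not state 32, and nothing below depends on it.

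**When assignment and receipt differ.** The two counts differ only for a patient who never takes the assigned bath or who bathes at another setting. A patient who starts the assigned bath and stops for discomfort is in the same arm under both rules.

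**Inputs for an illustration.** All are assumed, because the article gives neither a reaction rate nor a non-receipt rate:
- f: share of an arm that never takes the assigned bath, 2.5 to 10%. The upper end borrows the 10% loss allowance as a round figure only. In an arm of 36 this is 36 × 0.025 = 0.9 to 36 × 0.10 = 3.6 patients.
- p: reaction rate in those who bathe.
- b: reaction rate in those who do not bathe but may still take the basic treatment.

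Reported rate = (1 − f) × p + f × b.

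| p | b | f = 0 | f = 2.5% | f = 5% | f = 10% |
|---|---|---|---|---|---|
| 10% | 0 | 10.0% | 9.75% | 9.5% | 9.0% |
| 20% | 0 | 20.0% | 19.5% | 19.0% | 18.0% |
| 10% | 5% | 10.0% | 9.875% | 9.75% | 9.5% |

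The largest loss in the 10% rows is 36 × (0.10 − 0.09) = 0.36 of one patient.

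**Bath arm against basic treatment.** Take p = 30%, with 5% both in the basic arm and in the unexposed. The true difference is 25 points. At f = 10% it is 0.9 × 30 + 0.1 × 5 − 5 = 22.5 points. The difference shrinks by the share f. With 36 per arm and two-sided 0.05, power is 81% at f = 0. At f = 10% it is 75% by assignment and 79% by bath received.

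**Two bath conditions, true rates 25% and 10% (15 points), f = 10%:**
- Non-receipt only in the less tolerated arm, b = 0: 22.5 − 10 = 12.5 points. With b = 5%: 22.5 + 0.5 − 10 = 13.0.
- Non-receipt only in the better tolerated arm, b = 0: 25 − 9 = 16 points, which is larger than the truth.
- Non-receipt in both arms, b = 0: 22.5 − 9 = 13.5 points.

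So the difference between arms can err either way.

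**Laboratory values.** If a share g of an arm has only a baseline value, carry-forward gives those patients a change of zero. The reported mean change is (1 − g) times the mean change in those tested. The article gives no g.

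**The case against.** The strongest case against is that this is mostly silence. The article is condensed, safety has its own section with its own cited source, and a separate safety population is often left to the full protocol or analysis plan. No sentence says outright that reactions are grouped by assigned bath, and none rules out a treatment-received set. That is a fair reason for a low grade, but it does not remove the point. The article fixes a rule for all data, and a later plan with a treatment-received safety set would contradict the published sentence.

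The second objection is that departures should be few, and this largely stands. Patients are inpatients and nurses prepare each bath. Menstruation during hospitalisation is an exclusion, and a single missed bath does not change the group of a patient who has bathed at least once.

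A reader might also infer more than the documents support:
- **That harm is diluted as a matter of fact.** It is diluted only if some patients do not receive the assigned bath, and the article predicts no such number.
- **That the 10% loss allowance is the dilution rate.** It is loss, not non-receipt. Follow-up runs monthly for 6 months after treatment, and nothing says that losses precede the first bath.
- **That patients bathe at another arm's setting.** If 4 of 36 did, 15 points would become (0.25 × 32 + 0.10 × 4) / 36 − 0.10 = 13.3 points, but no switching is described.
- **That the bias always hides harm, or leans toward equal safety.** The 16-point example shows otherwise.
- **That the unexposed are free of reactions.** They may still react to the basic treatment.

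**Conclusion.** The point holds as a minor one. As written, section 2.7 counts safety by assignment and carries baseline laboratory values forward, although safety by bath condition is an aim. For any one bath arm, this can lower the reported reaction rate when some patients never bathe and the unexposed react less often than bathers.

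The effect is nil with full receipt. Under the assumed 2.5 to 10% non-receipt it is 0.25 to 1.0 percentage point on a true 10% rate if the unexposed have no reactions, and half of that if 5% of them react. For comparisons between arms, neither size nor direction can be fixed from the documents, because both depend on where the non-receipt falls.

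**What to change.** In section 2.7, limit the intention-to-treat and carry-forward sentences to the efficacy outcomes, and add a safety rule along these lines:

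> *Adverse events, adverse reactions and laboratory safety will be analysed in patients who received at least one assigned study treatment, grouped by the bath condition actually received and using observed laboratory values. Patients assigned to a bath who took only the basic treatment will be listed separately. A table by assigned group will be given as support.*

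The separate listing matters. Merging those who declined a bath into the basic treatment arm would add a self-selected group to a randomised comparator. The rule should also say in advance how a patient who receives more than one bath condition is classified, should that occur.

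The cost is a few lines of text and one extra table. The downside is that the main safety groups are no longer strictly as randomised, which the by-assignment table covers. No clinical procedure changes.

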**Methods::**

In this randomized controlled trial, we planned to recruit 288 hospitalized atients with psoriasis vulgaris aged 18 to 65 years. All participants who meet the inclusion criteria will be randomly assigned to the observation group, the control group, or the basic treatment group. The observation group will be divided into 6 sub-groups according to water temperatures and bath concentrations, designated as observation groups 1 to 6. Thirty-six participants will be assigned to each group. The basic treatment group will be given co-qingdai capsule, po 2 g tid; compound glycyrrhizin tablet, po 75 mg tid; AA Skincare jojoba Oil, us.ext qd. The observation group will be given a Chinese herbal bath at the same time as the basic treatment. The control group will be given ozone hydrotherapy at the same time as the basic treatment. The entire treatment course will last for 2 weeks. The following parameters will be compared in each group, before and 2 weeks after treatment: the psoriasis area and severity index score (PASI), pruritus score, clinical efficacy, and dermatology life quality index score (DLQI); serum levels of serum VEGF, TNF-α, IL-23, and IL-17; and confocal laser scanning microscope images.

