#### Trial course and follow-up

2.3.7

The treatment course will last 2 weeks, and the outcomes will be recorded before treatment and during the second week of treatment. After the 2 weeks of treatment, the patients will be followed up once per month for the next 6 months.

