### Primary outcome

2.4

Psoriasis area and severity index^[13]^ scores will be evaluated as the primary outcome. The PASI is a reliable, reproducible, and responsive instrument. This index has good internal consistency, intra-observer reliability, and inter-observer reliability, and is considered as the gold standard for assessing the severity of cutaneous manifestations in psoriasis. Therefore, this index will be used as our primary outcome.^[14]^

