## Discussion

3

Psoriasis is a common chronic recurrent skin inflammatory disease. Psoriasis vulgaris plays a major role in the psoriasis. In the process of clinic, patients with psoriasis vulgaris are also the most common. The visiting time of patients is often in the progressive stage of psoriasis vulgaris, during this period, the original lesions gradually expand, or even fuse into pieces, new lesions continue to appear, which has the most serious impact on patients. With the gradual understanding of the pathogenesis of psoriasis and the continuous improvement of medical level, psoriasis has made great progress in treatment measures, but it is still in the stage of disease control and cannot be completely cured. Most patients need lifelong treatment. Long-term treatment, heavy economic burden, and easy recurrence have become the main factors affecting the quality of life of patients. Therefore, through the study of optimizing the treatment plan of psoriasis, reducing the economic burden of patients and delaying the time of recurrence, it is very important to formulate a reasonable treatment and follow-up plan, take targeted intervention measures and improve the quality of life of patients. The Chinese herb bath can achieve ideal curative effect by penetrating the drugs with warm effect into the skin or meridian points and directly into the meridians and blood vessels, acting on the focus site. After soaking in the bath of Chinese medicine liquid, the skin can remove pollutants such as exudates, crusts and scales, and has the effects of moisturizing and relieving itching, clearing heat and cooling blood, detoxification and convergence; Chinese medicine liquid can dilate the capillaries of patients and improve local microcirculation, promote metabolism, accelerate the repair of affected tissue, and promote the regression of skin lesions. In clinic, the use of Chinese herb bath, or Chinese herb bath combined with other therapies in the treatment of psoriasis is quite common, with high efficiency, definite curative effect, few adverse reactions and good patient compliance.

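### With only a baseline and a week-2 reading, carrying the last observation forward gives every patient without a week-2 PASI zero improvement, which shrinks real arm differences and can create false ones

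*Protocol article*

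**What the plan says.** The primary outcome is PASI: "Psoriasis area and severity index^[13]^ scores will be evaluated as the primary outcome" (section 2.4). Section 2.7 sets the analysis population and the missing-data rule in consecutive sentences: "All data will be analyzed according to the intention to treat principle" and "The missing value will be dealt with by carrying forward the most recent observation to the end point". It then prescribes paired and independent-sample t tests, or rank-sum tests, on the completed data.

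Section 2.3.7 gives the timing: "the outcomes will be recorded before treatment and during the second week of treatment". The Abstract agrees that there are two occasions: "The following parameters will be compared in each group, before and 2 weeks after treatment". Sections 2.5.3 and 2.5.4 name the same two for the serum markers and the microscopy. No reading between baseline and week 2 appears in the text. Section 2.2.3 expects some loss: "the necessary estimated loss rate is 10%, and the total sample size is 288 cases, with 36 cases per group".

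Under section 2.3.1 every patient in every arm receives the three-part basic treatment.

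**The concern.** Carrying the last observation forward is usually described as using the latest on-treatment value. Here there is none before week 2, so the most recent observation for a patient without a week-2 PASI is the pre-treatment score. The rule is in effect baseline carried forward, and it imputes a change of exactly zero.

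That is not a neutral guess in a trial where even the basic group is actively treated. The imputed zeros pull each arm's mean improvement towards zero in proportion to its loss. Equal loss dilutes a true difference. Unequal loss turns the difference in loss into an apparent difference in effect. The trial is meant to rank bath temperatures and concentrations, and a bath is stopped when the patient reports discomfort (section 2.3.5), so the factors under test could also influence who is assessed at week 2.

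**Working it through.** **The plan's own figures.** 8 groups × 36 = 288, as stated. 36 fits 32 evaluable patients with 10% loss (32 / 0.9 = 35.6, rounded up to 36). The 32 itself cannot be checked, because the article gives no effect size, SD or power. Expected loss is 0.10 × 36 = 3.6 per group and 0.10 × 288 = 28.8 overall.

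**Inputs from the article.** 36 per group; 10% loss; t tests; significance at 0.05 (two-sided assumed); two readings.

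**Inputs assumed, because the article gives none.** PASI SD of 1 unit at both times; baseline to week-2 correlation r = 0.5; mean improvement μ of 1 to 1.5 SD; arm-specific loss as shown; loss unrelated to the scores within an arm.

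**Step 1: mean.** A fraction d of an arm is assigned zero change, so expected improvement is (1 − d)μ. The contrast between arms A and B becomes (1 − dA)μA − (1 − dB)μB.

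**Step 2: equal loss of 10%, true difference 0.5 SD.**
- Estimated difference: 0.9 × 0.5 = 0.45 SD.
- Reference, 32 completers per arm: 0.5 × √(32/2) = 2.0 against a critical value of 1.96, so power is about 50%.
- Variance under carry-forward: the week-2 score has 1 + d(1 − d)μ². The change score has (1 − d) × 2(1 − r) + d(1 − d)μ², which is 0.9 + 0.09μ² here.
- Arms improving by 1.0 and 1.5 SD, week-2 score: variances 1.09 and 1.2025, mean 1.146; SE = √(2 × 1.146/36) = 0.252; 0.45/0.252 = 1.78; power about 43%. Change score: variances 0.99 and 1.1025, mean 1.046; SE 0.241; ratio 1.87; power about 46%.
- Arms improving by 1.5 and 2.0 SD, week-2 score: variances 1.2025 and 1.36, mean 1.281; SE 0.267; ratio 1.69; power about 39%. Change score: variances 1.1025 and 1.26, mean 1.181; SE 0.256; ratio 1.76; power about 42%.
- Range: about 39–46%. With equal true effects and equal loss the contrast is zero, and simulated type I error is about 5%.

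**Step 3: unequal loss, no true difference.** The spurious difference is (dB − dA)μ. Simulated type I error at 36 per arm, over μ = 1 to 1.5 SD and both score types:

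| Loss, A v B | Spurious difference (SD) | Type I error |
|---|---|---|
| 10% v 10% | 0 | about 5% |
| 7.5% v 12.5% | 0.05 to 0.075 | about 5–6% |
| 5% v 15% | 0.10 to 0.15 | about 7–9% |
| 5% v 20% | 0.15 to 0.225 | about 9–15% |

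Hand check of one cell (5% v 15%, μ = 1.5, week-2 score): variances 1 + 0.0475 × 2.25 = 1.107 and 1 + 0.1275 × 2.25 = 1.287, mean 1.197; SE 0.258; 0.15/0.258 = 0.58; rejection probability Φ(−1.38) + Φ(−2.54) ≈ 0.084 + 0.006 = 9%.

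**Step 4: the same in PASI points.** With an assumed SD of 5 and r = 0.6, loss of 5% v 15% gives a spurious 0.3, 0.5 or 0.8 points for improvements of 3, 5 or 8 points. Simulated type I error is 6.5–7.6% at 5 points and 9.1–10.2% at 8 points. The conclusion does not depend on the SD scale.

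**The case against.** **Assessment may continue after a bath is stopped.** Section 2.3.5 returns the patient to the ward; it does not remove the patient from the trial. Participants are inpatients on a two-week course, so week-2 PASI may be obtained for most of them. This stands: the rule affects patients without a week-2 reading, not everyone who stops bathing, and unequal loss is a possibility, not a documented fact. The dilution at equal loss does not need it.

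**Counting dropout as no improvement can be a legitimate conservative target.** It can, if declared. The article declares no such target; it states carry-forward under intention to treat. The type I error figures are relative to the effect had patients stayed on treatment.

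**Figure 1 might show a week-1 reading.** It was not available. A week-1 value would soften the point, though it would still stand in for week 2.

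**The remedy makes assumptions too.** With only a baseline to impute from, multiple imputation by arm is close to a baseline-adjusted complete-case analysis. It gives missing patients the improvement of completers in their arm, which can favour a poorly tolerated arm. This stands, and is why carry-forward is kept as a sensitivity analysis.

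**Missing-data detail belongs in the analysis plan.** That would answer an omission. Here the rule is stated.

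**Conclusion.** The point holds for week-2 PASI. On the visible text, the stated rule assigns zero change to every patient without a week-2 reading. At the protocol's own 10% loss, equal across arms, the cost is a 10% shrinkage of any true difference and a drop in power from about 50% to about 39–46% for a 0.5 SD difference, with type I error near 5%. Inflation of type I error requires unequal loss: slight at 7.5% v 12.5%, about 7–9% at 5% v 15%, and 9–15% only at 5% v 20%, where average loss (12.5%) exceeds the planned 10%. Improvement, correlation and arm-specific loss are assumptions, and the sizes apply to the t test.

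Three stronger readings are not supported:
- A reader might infer that the rule hides relapse over six months. The article says "the patients will be followed up once per month for the next 6 months" and, in the Discussion, that "easy recurrence have become the main factors affecting the quality of life of patients", but it names no outcome for the monthly visits, so there is nothing definite to carry forward.
- A reader might work out a larger error for pooled bath sub-groups, such as 108 v 108. The article describes eight groups of 36 and no pooling.
- A reader might add that single imputation understates uncertainty. In simulation at 10% loss the between-arm model standard error matched the empirical one (1.23 v 1.22 PASI points). The harm is to the estimate.

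**What to change.** Change section 2.7 as follows.

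1. Remove carry-forward as the primary rule.
2. State that week-2 PASI is sought for every randomised patient, including those who stop bathing, and that missing readings are reported by arm with reasons.
3. Analyse observed week-2 PASI with a baseline-adjusted model (ANCOVA). For values still missing, use multiple imputation by arm under a stated missing-at-random assumption.
4. Keep baseline carried forward as a sensitivity analysis, labelled as counting dropout as no improvement.

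If Figure 1 contains a reading between baseline and week 2, section 2.3.7 should say so and the imputation should use it.

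The cost is a change of wording and a little more analysis work; multiple imputation is standard in common statistical software. No visits are added, because the patients are inpatients and the week-2 assessment is already planned. The downside is reliance on missing at random, which item 4 checks. The change should be made before the data are analysed.

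### The between-group tests fixed in Section 2.7 use no baseline covariate and do not say whether week-2 PASI or its change is tested; a pre-specified ANCOVA would be more precise

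*Protocol article*

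**What the plan says.** Section 2.4 makes "Psoriasis area and severity index" scores the primary outcome without saying whether the analysed quantity is the week-2 score or the change. Section 2.3.7 states that "the outcomes will be recorded before treatment and during the second week of treatment", so a pre-treatment PASI exists for each participant. The Methods part of the abstract says "The following parameters will be compared in each group, before and 2 weeks after treatment" and lists PASI, pruritus, DLQI and the cytokines, again without defining the analysed variable.

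Section 2.7 then names the tests for quantitative outcomes:

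- within a group, the paired t "test will be used for intra-group comparison";
- between groups, the independent-sample t "test will be used for inter-group comparison";
- "If the variance is uneven, the approximate" t test takes over;
- "If the sample is not normally distributed, the rank-sum test (non-parametric) will be applied".

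P "values less than .05 will be considered as statistically significant". No covariate is mentioned. Section 2.3.1 gives the three-part basic treatment to all participants in all eight arms.

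**The concern.** Three features of Section 2.7 work against the primary comparison.

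- **No covariate.** A patient's PASI two weeks after entry is likely to depend on PASI at entry, and Section 2.2.1 sets no PASI limits that would narrow the spread. A between-group test without baseline as a covariate leaves that explainable variation in the error term and lets chance differences at entry pass into the estimate.
- **A data-dependent test.** Because the test follows from normality and variance checks, different arm pairs or outcomes can end up with different tests, and a t test and a rank-sum test do not address the same quantity. With the analysed variable also undefined, the primary analysis is not one fixed procedure.
- **Within-arm P values.** Change inside one arm mixes the basic treatment, inpatient care, regression to the mean and any bath effect. It says nothing about the bath without a comparator.

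At stake are precision on the primary outcome with 36 patients per arm, and clarity about which result is the randomised one.

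**Working it through.** **Inputs from the article.** Eight arms of 36 (8 × 36 = 288, as Section 2.2.3 states) and 10% loss, so 36 × 0.9 = 32.4, about 32 evaluable per arm. Significance level 0.05 (Section 2.7).

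**Assumptions.** A two-sided test; a true difference of d = 0.5 SD; equal SD at both times; and a baseline/week-2 correlation r between 0 and 0.7. The article gives no effect size, SD, power or correlation, so its 36 per arm cannot be rebuilt and serves only as the sample size.

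**Variance of the group difference**, relative to a week-2 t test:

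- week-2 score: 1
- change score: 2(1 − r)
- ANCOVA: 1 − r²

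The ratio of ANCOVA to change score is (1 − r²)/[2(1 − r)] = (1 + r)/2.

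**Power.** The noncentrality is d/√(2f/n), with f the variance factor, referred to the noncentral t. For the week-2 test at n = 32 it is 0.5/√(2/32) = 2.0, giving 50%. For ANCOVA at r = 0.5 it is 2.0/√0.75 = 2.31, giving 62%.

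| r | ANCOVA factor | Week-2 t test | Change-score t test | ANCOVA | 36 per arm with ANCOVA is worth |
|---|---|---|---|---|---|
| 0.3 | 0.91 | 50% | 38% | 54% | 36/0.91 = 40 |
| 0.5 | 0.75 | 50% | 50% | 62% | 36/0.75 = 48 |
| 0.7 | 0.51 | 50% | 72% | 79% | 36/0.51 = 71 |

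The last column is relative to a week-2 t test. Against a change score the variance ratios are 0.65, 0.75 and 0.85, so the gain narrows as r rises: at r = 0.7 it is about 7 points, compared with 29 points over the week-2 test.

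**Cost of the covariate.** Estimating the slope in a two-arm comparison inflates the variance by about 1 + 1/(2n − 4) and takes one degree of freedom. At n = 32 and r = 0.5, power falls from 62.3% to 61.6%. At r = 0, with n = 36 and d = 0.66 SD (the effect giving 80% power by the normal approximation), the t-based figures are 78.9% unadjusted and 78.3% for ANCOVA, a loss of 0.6 points.

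**Chance imbalance.** With 36 per arm the baseline difference between two arms has SD √(2/36) = 0.24 baseline SD.

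- For one given pair, the chance that it exceeds 0.25 SD is 29%. The chance that it exceeds 0.5 SD is 2[1 − Φ(0.5/0.2357)] = 3%.
- Across eight arms, the expected gap between the highest and lowest baseline mean is 2.85/√36 = 0.47 SD.
- At r = 0.5, a 0.5 SD imbalance shifts the week-2 difference by 0.5 × 0.5 = 0.25 SD, and the type I error given that imbalance is about 15%. A change score has the same size of error in the opposite direction.
- Averaged over all imbalances, 20,000 simulated trials gave a type I error near 5% for all three analyses.

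**The case against.** An unadjusted t test in a randomised trial is valid. Chance imbalance is already reflected in its standard error, and the simulation bears this out. Covariates are often left to the analysis plan, which is not shown. This stands as a limit: the point concerns efficiency and clarity, not an invalid test. It does not dispose of the point, because Section 2.7 is not silent. It names the tests and the rule for choosing among them, and none is adjusted.

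Three stronger readings are tempting but not supported.

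- A reader might infer that paired tests replace the between-group comparison. They do not; Section 2.7 assigns the independent-sample test to that purpose in the same sentence.
- A reader might infer that baseline PASI goes unused in the between-group test. The article does not settle this. If change is analysed, baseline is used, though less efficiently than in ANCOVA.
- A reader might infer that efficacy will be judged from eight within-arm P values. The article never says so; the risk is only that they could be read that way.

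The size of the gain also rests on an assumed correlation. And because Section 2.7 specifies intention to treat with the last observation carried forward, 36 per arm may be analysed. The week-2 test then has 55% power (noncentrality 0.5/√(2/36) = 2.12), while the variance ratios are unchanged.

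**Conclusion.** The point holds as a recommended improvement. The tests fixed in Section 2.7 control type I error overall but give away precision, leave the analysed variable undefined and let the data choose the test. Under the assumptions stated, ANCOVA gains about 4, 12 or 29 power points over a week-2 t test at r = 0.3, 0.5 or 0.7, and about 16, 12 or 7 points over a change-score t test. At r = 0 it gains nothing over the week-2 test and loses a fraction of a point.

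It would be too strong to say that ANCOVA removes baseline imbalance at no cost. It adjusts for imbalance in the baseline value of that outcome only, uses a degree of freedom and assumes an approximately linear common slope. The within-arm tests are planned in addition to the randomised comparison, but with basic treatment given in every arm they cannot show a bath effect.

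**What to change.** Reword Section 2.7 as follows.

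- Name one primary analysis: week-2 PASI regressed on arm with baseline PASI as covariate, with heteroscedasticity-robust standard errors, and adjusted differences reported with confidence intervals.
- Use the same model for the other continuous outcomes that have baseline values: pruritus, DLQI and, in the 22 sampled patients per group, the cytokines. Decide any log transformation in advance.
- Drop the choice of test by normality and variance checks; a rank-based analysis can remain as a stated sensitivity analysis.
- Report within-arm changes descriptively, without P values.

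No new data are needed, since baseline values are already collected. The statistical cost is one degree of freedom (about 0.6 power points if r is 0) and reliance on an approximately linear common slope, which can be checked in a sensitivity analysis.
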